**Randomization and power/sample size.** Our protocol utilizes two groups, 0°-HOB and 30°-HOB, and allows us to offer enrollment to consecutive eligible patients. To assure balance in the treatment group throughout the course of enrollment, we will use block randomization with a block size of 4 and an allocation ratio of 1:1. This scheme has been implemented in the *Unity* computerized enrollment procedure that only shows the random assignment for a single given participant to the user and may scramble subject enrollment numbers to ensure randomization balance. Future assignments cannot be predicted by study personnel because of the block assignment made together with assignments at all sites, and this effectively mitigates the risk for selection bias that might occur if anticipated group assignment were able to influence enrollment decisions.

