### Endpoints.

Primary Endpoint: The percentage of patients with early neurologic deterioration (END) is our primary outcome. END is defined as a two or more point worsening ( $\geq 2$ ) in the NIHSS score in comparison to the time-0 NIHSS score at the time of positioning intervention termination (placement of the patient on the catheterization table or immediately prior to the time of elective induction/intubation for thrombectomy in centers utilizing general anesthesia). Not deteriorating (being stable) is defined as less than 2-point NIHSS worsening ( $< 2$ ) or NIHSS score improvement in comparison to the time-0 NIHSS score during the head position intervention.

We expect to see at most 5% of END participants in the 0° head position group, compared to 20% of END patients in the 30° head position group (15% lower deterioration). Our group-sequential design allows for early stopping due to futility or efficacy and is based on a two-sample two-sided proportion test as implemented in East 6.0 (Cytel, Cambridge, MA) with type I error  $\alpha=0.05$  and 80% power; it incorporates 3 interim analyses and 1 final look at the data which results in a sample size of  $n = 182$ . Interim analyses are planned with equal spacing after cases have been enrolled/observed for the primary endpoint (Table 2). The Lan-Demets alpha and beta spending approach with O'Brien-Fleming

boundaries are used both for futility and efficacy interim monitoring. Absence of primary endpoint evaluation will be counted as an END event so that all randomized participants will have a determined primary endpoint available for analysis, allowing for an intent-to-treat analysis with no primary endpoint attrition.

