Analysis Plan for Aim 1 (primary efficacy endpoint); Hypothesis: *Patients with large artery occlusions placed in a 0°-HOB position will experience less early neurological deterioration than those in the 30°-HOB elevation group.* We will apply sequential testing in both patient groups (Table 2). As an example, the first look in the protocol is performed when 46 participants are enrolled/have their primary outcome evaluated; if the z-value associated with the test of equality of proportions in both arms is above 4.333 or below -4.333 the trial will be stopped early for efficacy (one group is clearly superior with respect to the primary outcome), whereas if that z-value is in the interval (-0.007, 0.007), the trial will be stopped early for futility (groups are essentially identical in outcome). If the z-value falls within the intervals (-4.333, -0.007) or (0.007, 4.333), the trial will continue until the next look at the data. Note that for the primary endpoint, absence of evaluation is counted as deterioration and that, consequently, all randomized participants will have a determined primary endpoint available for the analysis; therefore, intent-to-treat principles will support our primary data analysis. We will use unadjusted Cox proportional-hazards modeling to compare and Kaplan-Meier curves to visualize the rate of early neurological deterioration (> 2 NIHSS points change from baseline) in the two groups. The number at risk and censored in each group will be reported in the Kaplan-Meier survival curves every 10 minutes. Overall rates of END and according to group will be reported as frequencies and percentages and compared between groups with Fisher's Exact test. The number needed to harm will be estimated as the inverse of the absolute risk increase (ARI) = 1/ARI.

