**Table 2: Stopping Boundaries for the Sequential Design.**

| Look # | Sample Size
MT Subjects | Stopping Boundaries (Extended Protocol) |        |                              |        |
|--------|----------------------------|-----------------------------------------|--------|------------------------------|--------|
|        |                            | Efficacy Z
(lower, upper)            |        | Futility Z
(lower, upper) |        |
| 1      | 46                         | 4.333                                   | -4.333 | 0.007                        | -0.007 |
| 2      | 92                         | 2.963                                   | -2.963 | 0.374                        | -0.374 |
| 3      | 138                        | 2.359                                   | -2.359 | 1.261                        | -1.261 |
| 4      | 182                        | 2.014                                   | -2.014 | 2.014                        | -2.014 |

Analysis Plan for Process Evaluation. Most of the process evaluation components (Table 1) naturally render themselves to description and categorization. Noteworthy exceptions are aspects relating to intent-to-treat vs. per-protocol received treatment, and control of head positioning assignment. The data collected will enable generation of statistical quality control charts if necessary, to monitor the proportion of non-conforming patients (delivered treatment different from assigned protocol) over time. Should control charting be necessary, they will be assembled by ZODIAC independent biostatisticians and provided to Drs. [name] and [name] (the study's protocol fidelity and implementation science experts) as an ongoing monitoring effort. The upper and lower control levels of these charts will allow a ready assessment of whether deviations over time or between hospitals are coincidental or driven by some real difference or shift in hospital procedures.

Analysis Plan for Aim 2 (secondary aim assessing safety). Serious adverse events (SAE) that will be monitored closely in this trial include: 1) Severe neurological deterioration; 2) hospital acquired pneumonia; and, 3) death. Analyses will be descriptive and include rates for SAEs by study cohort.

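### The Aim 1 plan explains a futility stop as near-identical outcomes, a reading that a superiority design without an equivalence margin cannot support

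*Supplement*

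**What the plan says.** All references are to protocol version 2.0. Under Endpoints, the design is a "two-sample two-sided proportion test as implemented in East 6.0 (Cytel, Cambridge, MA) with type I error $\alpha=0.05$ and 80% power", and the planning rates are "at most 5% of END participants in the 0° head position group, compared to 20% of END patients in the 30° head position group", a difference of 15 points. Lan-DeMets spending with O'Brien-Fleming boundaries serves both efficacy and futility, with three interim looks and a final look at 182 patients.

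The Analysis Plan for Aim 1 then illustrates the Table 2 rule: "As an example, the first look in the protocol is performed when 46 participants are enrolled/have their primary outcome evaluated". In that example each kind of stop is given a meaning. Efficacy is explained as clear superiority of one group. For |z| below 0.007, "the trial will be stopped early for futility (groups are essentially identical in outcome". The plan offers no other meaning for a futility stop.

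Table 2 lists z-values without interpretation. The futility zones are |z| below 0.007 (n=46), 0.374 (n=92) and 1.261 (n=138); the look-3 row reads "3 | 138 | 2.359 | -2.359 | 1.261 | -1.261". The Data Safety Monitoring Plan (Plans for Interim Efficacy and Futility Analyses) repeats the look-1 rule. It keeps the gloss on efficacy and drops the one on futility.

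**The concern.** A futility boundary obtained by spending beta against a 15-point difference says that the planned effect is unlikely to be shown if the trial goes on. It does not bound the true difference near zero. That would need a margin and an interval lying inside it, and the plan has neither. The Aim 1 analyses are group percentages, Fisher's exact test, an unadjusted Cox model and the number needed to harm; no confidence interval for the END risk difference is named.

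The monitoring board reports its futility findings to the principal investigator, the IRB and NIH. A pre-specified phrase that equates futility with sameness invites the conclusion that head position makes no difference, from data that may not exclude the effect the trial was built to find.

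**Working it through.** **Inputs.** END 5% v 20%, two-sided alpha 0.05, 80% power (Endpoints); efficacy and futility z-values (Table 2); "block randomization with a block size of 4 and an allocation ratio of 1:1" (Randomization), taken as 23, 46, 69 and 91 per arm. The 10-point differences below are assumptions; the documents give only 15 points.

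**1. The plan's own figure.** The fixed-sample size per arm is

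n = [1.96·√(2·0.125·0.875) + 0.8416·√(0.05·0.95 + 0.20·0.80)]² / 0.15² = 75.1, so 76.

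With continuity correction this becomes 88 per arm, or 176 in total. The efficacy boundaries inflate it by 1.020: 176 × 1.020 = 179.5, within 3% of 182. Simulated power at 182 is 79.6% with the correction and 83.5% without. Type I error is 0.0499 with non-binding futility and 0.0457 with binding futility. The boundaries and the sample size therefore stand.

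**2. Look 1, where the words are placed.** The statistic is z = (p2 - p1)/√(2p(1-p)/n), with p pooled. At 23 per arm, 2/23 v 3/23 already gives z = 0.474, and no one-event difference gives less than 0.295. So |z| below 0.007 means equal counts. For 3/23 in each arm (13.04%), the Wilson limits are 4.54% and 32.13%. Newcombe's interval for the difference is

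0 ± √[(13.04 - 4.54)² + (32.13 - 13.04)²] = ±20.9 points.

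For 2/23 in each arm it is ±19.2, and for 1/23 it is ±17.0. Each contains 15 points.

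**3. Look 3, if the same reading is applied there.** Take 4/69 (5.80%) v 8/69 (11.59%). Pooled p = 12/138 = 8.70%, the standard error is 4.80 points, and z = 5.80/4.80 = 1.21, inside the 1.261 zone. The Wilson limits are 2.28% to 13.98% and 5.99% to 21.25%, so the interval is

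- lower: 5.80 - √[(11.59 - 5.99)² + (13.98 - 5.80)²] = -4.1
- upper: 5.80 + √[(21.25 - 11.59)² + (5.80 - 2.28)²] = +16.1

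The Wald interval is -3.6 to +15.1. Both contain 15 points. These are ordinary fixed-sample intervals, not adjusted for the sequential looks.

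**4. How often futility stops the trial.** Binomial counts, pooled z, Table 2 boundaries, 0 v 0 counted as z = 0:

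| True END rates | Look 1 | Look 2 | Look 3 | Looks 1 to 3 | Non-significant at final look |
|---|---|---|---|---|---|
| 5% v 20% (planned) | 5.3% | 1.9% | 3.6% | 10.8% | 5.7% |
| 5% v 15% (assumed) | 10.7% | 5.4% | 12.8% | 28.9% | 14.7% |
| 10% v 20% (assumed) | 10.6% | 10.6% | 18.8% | 40.1% | 18.2% |

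The look-1 column needs an exact 23/23 split. Since 46 is not a multiple of 4, a 22/24 split is possible; equal proportions are then rare (0/22 v 0/24 or 11/22 v 12/24, for instance), and so are look-1 stops. Steps 2 and 3 show what a stop would mean and do not rest on these frequencies.

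**The case against.** The strongest reply is that the phrase belongs to look 1 alone. There, |z| below 0.007 means equal observed counts, so the words describe the observed result correctly. Table 2 adds no interpretation, the monitoring plan drops the gloss, and Aim 1 is framed as superiority with no similarity claim planned. Readers will also see END percentages by group.

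Much of this stands. No text attaches the phrase to looks 2 or 3, so step 3 is conditional. Not every futility result is as open as those shown: 5/46 v 5/46 at look 2 gives ±13.6, which excludes 15 points. What does not stand is that equal counts in 46 patients justify the wording. It is offered as the meaning of the stop, parallel to clear superiority for efficacy, and it serves as the plan's example of the whole rule.

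Two stronger readings are tempting. A reader might add final-look non-significance to the early stops, reaching 28.9 + 14.7 = 43.6% for 5% v 15% and about 58% for 10% v 20%, and take this as how often the plan would declare the positions alike. The documents do not support that: the sum is total non-rejection at an assumed effect, and the plan never labels a non-significant final result as identical. A reader might also infer that an equivalence margin is missing. None is needed, because no equivalence claim is planned.

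**Conclusion.** The point holds as a minor correction of interpretation. The gloss in the look-1 example is unsound even at look 1, where equal counts of one to three events per arm leave a 15-point difference inside the 95% interval. If carried to look 3, it would also cover an observed doubling of END.

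Futility stops the trial at look 1 in about 5% of trials under the planned rates and in about 11% under an assumed 10-point difference. Over looks 1 to 3 the figures are about 11%, and 29% to 40%. They assume pooled z, arms of equal size at each look and stopping whenever a boundary is met; the 10-point figures also depend on the chosen base rates. The boundaries, sample size and superiority test are not in error on this point.

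**What to change.** In the Analysis Plan for Aim 1, delete the parenthesis that explains the futility stop. In its place, state that a futility stop at any interim look means that superiority of either head position was not shown, and that it is not evidence of equivalence. Add that the END risk difference will be reported with its two-sided 95% confidence interval, whether the trial stops early or runs to 182.

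The cost is one sentence and one interval. Table 2, the sample size and trial conduct stay as they are, and no equivalence margin has to be set. The version history records enrolment under version 2.0 as closed, so if the plan can no longer be amended, the same reading and interval can go into the report.

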Early neurologic deterioration is common in hyperacute ischemic stroke, ranging from 15% to 37.5% in large clinical trials, and selection of HOB positioning may play an important role in its occurrence. However, to date, clinical trial protocols exploring numerous drug and device interventions have remained silent on HOB positioning. Mechanisms proposed for clinical improvement at 0°-HOB include favorable gravitational arterial flow conditions, recruitment of collateral arterial blood flow routes, and in the case of intravenous thrombolysis, improved clot-lytic interactions augmenting arterial recanalization. Collectively, these mechanisms have caused many to argue that 0°-HOB positioning should be among the first steps taken in large artery hyperacute ischemic stroke patient management. The goal of this efficacy study is to determine if 0°-HOB positioning in hyperacute ischemic stroke prevents neurological symptom worsening in large artery occlusion patients. The study will achieve these goals through use of a novel protocol enabling enrollment of consecutive large artery occlusion patients while maintaining compliance with management specified by national guidelines, stroke center certification requirements, and U.S. core measures. We will enroll hyperacute large artery patients with salvageable brain early into stroke symptoms, that are candidates for mechanical thrombectomy (MT) (n=182). Patients will be randomized to one of two groups: 1) 0°-HOB positioning; or, 2) 30° HOB positioning. The primary endpoint will be early neurological deterioration (stroke symptom worsening) defined as an increase of 2 or more points from baseline (pre-intervention) National Institutes of Health Stroke Scale (NIHSS) score during the positioning period. These data will be employed to meet the following specific aims:

Aim 1 (primary efficacy endpoint): To identify if use of 0° HOB positioning is associated with clinical stability in hyperacute ischemic stroke. Hypothesis: *Patients with large artery occlusions placed in a 0° HOB position ( $V_1$ ), (superiority hypothesis), will experience less early neurologic deterioration within the time prior to thrombectomy, than those in the 30° HOB elevation group ( $V_c$ ), or  $H_0: V_1 = V_c$  versus  $H_A: V_1 < V_c$ .*

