Severe neurological deterioration (SND) is defined as at least a 4-point increase ( $\geq 4$ ) in the NIHSS from the time 0 NIHSS baseline. Our NIHSS serial assessments will allow for early detection of neurologic change in our subjects should it occur. SND is a severe form of deterioration, and consequently, our provision for early trial stopping is a safety measure. Because SND can be due to a number of different factors that may or may not be associated with this protocol, incidents of SND will also be reviewed by the Data Safety Monitoring Board (DSMB) as described below, and adjudicated to the intervention or other factors as indicated by their findings.

Hospital acquired pneumonia (HAP). The American Thoracic Society/Infectious Diseases Society of America (ATS/IDSA) guidelines will be used, defining pneumonia as requiring onset of a new or progressive infiltrate on pulmonary imaging within 72 hours, along with at least two of the following: 1) Fever  $\geq 38^{\circ}$  C; 2) purulent sputum; 3) leukocytosis or leukopenia; and/or, 4) decline in oxygenation. Based on our pilots, we are excluding cases from enrollment that are high risk for pneumonia; because these cases are kept NPO for thrombectomy, this will further reduce aspiration risk. We therefore believe that pneumonias will be rare and because of this, we believe that exposure to unnecessary additional chest imaging would add both increased cost and unnecessary radiation exposure, especially since stroke patients often require repeat neuroimaging. Instead, excellent nursing assessments will serve as triggers to inform the need for additional chest imaging in the case of pulmonary deterioration. Because pneumonia may be due to a number of different unassociated factors, pneumonia events will be DSMB reviewed and adjudicated to the intervention as indicated.

Death. Death occurring during the active protocol phase, throughout hospitalization, or within 3 months from enrollment will be monitored, and incidents adjudicated by the DSMB. Death may be associated with a number of unassociated factors, therefore the DSMB will carefully determine study association.

Other AEs detected will be DSMB reviewed and reported as related or unrelated to study procedures.

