All the safety outcome analyses will be executed in the intention-to-treat population. We will use unadjusted Cox proportional-hazards modeling to compare and Kaplan-Meier curves to visualize the rate of severe early neurological deterioration ( $> 4$  NIHSS points change from baseline) in the two groups. The number at risk and censored in each group will be reported in the Kaplan-Meier survival curves every 10 minutes. Overall and enrollment group rates of SND will be reported as frequencies and percentages and compared between groups with Fisher's Exact test. The number needed to harm for SND will be estimated as the inverse of the absolute risk increase (ARI) =  $1/\text{ARI}$ . Rates of hospital-acquired pneumonia, discharge, 90-day participant's death, post-discharge stroke, and symptomatic intracerebral hemorrhage post-reperfusion treatment will be reported in frequencies and percentages; these will be compared between groups using Fisher's Exact test together with odds ratios and the corresponding 95% confidence intervals and p-values from unadjusted logistic regression models that include randomization assignment as the predictor.

Pre-Specified Exploratory Endpoints: As discussed, END is the primary endpoint for this clinical trial and is measured proximally, at the termination of the intervention monitoring period. Our rationale for not utilizing a post-thrombectomy 90-day outcome is twofold: First, head positioning should not be deemed a "treatment" for LVO stroke; instead, head positioning is a rescue procedure similar to other medical care that is utilized to stabilize, optimize, and ensure both patient safety and optimal outcomes. The impact of a rescue procedure such as head positioning is best measured during the time it is implemented to determine its efficacy in supporting and optimizing patient condition. Second, thrombectomy is a highly effective definitive treatment for large vessel occlusion stroke patients. The tremendous effect size of thrombectomy may likely override any benefit of other interventions, including

head positioning, however this remains unknown at this time. In summary, we aim to determine the efficacy of head positioning as a simple rescue procedure, making measurement of END at the time of positioning on the catheterization lab table for thrombectomy (or immediately prior to elective induction/intubation in sites using general anesthesia for thrombectomy) our choice as the study primary endpoint.

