#### Procedures for Identifying, Reviewing, and Reporting Adverse Events and Unanticipated Problems to IRB and NIH

Safety is a secondary aim of this study and will be examined in this larger, more generalizable sample of patients. Specifically, SAEs that will be monitored closely in this trial include: 1) Severe neurological deterioration (SND) defined as a deterioration of  $\geq 4$  points on the NIHSS from the time-0 NIHSS; 2) hospital acquired pneumonia (HAP) as defined by the American Thoracic Society/Infectious Disease Society of America; and, 3) death. As SAEs occur, the DSMB, IRB and NIH will be notified by the PI. The DSMB Chair will convene a special called meeting (as described previously) to determine whether the SAE should be adjudicated to the intervention or other unrelated cause. The DSMB will follow the methods for meeting conduct as described previously in this document, along with the written report methods specified. Beyond individual SAE review, the DSMB will examine analyses as directed by the statistical plan. The DSMB will formally report their findings to the PI, IRB and NIH.

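### The Cox and Kaplan-Meier sentences set the END and SND events at more than 2 and more than 4 NIHSS points, while the endpoints are defined as at least 2 and at least 4

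*Supplement*

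**What the plan says.** All references are to protocol version 2.0 in the Supplement.

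**END.** The Endpoints section states that "END is defined as a two or more point worsening" relative to the time-0 NIHSS, assessed when positioning ends. It classes worsening of less than 2 points, and improvement, as stable. The Specific Aims use the same threshold of 2 or more. The Analysis Plan for Aim 1 then announces unadjusted Cox modelling, with Kaplan-Meier curves to "visualize the rate of early neurological deterioration (> 2 NIHSS points change from baseline) in the two groups". A little further on, the same paragraph says: "Overall rates of END and according to group will be reported as frequencies and percentages and compared between groups with Fisher's Exact test".

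**SND.** The Analysis Plan for Aim 2 states: "Severe neurological deterioration (SND) is defined as at least a 4-point increase". The adverse event section of the Data Safety Monitoring Plan agrees: "Severe neurological deterioration (SND) defined as a deterioration of" 4 or more points. The Cox/Kaplan-Meier sentence in the Aim 2 plan promises to "visualize the rate of severe early neurological deterioration", and the parenthesis that follows prints the threshold as greater than 4 "NIHSS points change from baseline) in the two groups".

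Nothing in the plan says that a stricter event is intended for the time-to-event models. Version 1.0 has the same sentences, so version 2.0 carried them over.

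**The concern.** The NIHSS is scored in whole points, so *more than 2* means 3 or more and *more than 4* means 5 or more. The Cox/Kaplan-Meier sentences use the endpoint names but attach a different threshold to them. An analyst who programs the parentheses as printed would produce a hazard ratio and curves for an event that is not the defined endpoint, next to Fisher's tests on the endpoint as defined.

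Two consequences follow. The report could show two END thresholds, and two SND thresholds, under one label each. And while both readings stay open, the model threshold could be settled after the data are seen. The primary endpoint and the first-listed safety event are both involved.

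**Working it through.** **Step 1. The plan's own design figures.** The sample size of 182 and the Table 2 boundaries rest on END proportions of 5% and 20% (Endpoints section), with END defined as 2 or more points.
- Numerical integration of the Table 2 efficacy boundaries gives a two-sided type I error of 0.0499 with futility ignored, which matches the stated 0.05.
- A fixed design for 5% versus 20% at 80% power needs 76 per arm (152), or 88 per arm (176) with continuity correction. With a sequential inflation of 1.081 these become 152 × 1.081 = 164 and 176 × 1.081 = 190.
- The stated 182 lies between the two and is not reproduced exactly. Simulating the Table 2 rule with 91 per arm gives about 83.5% power, above the stated 80%.

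Nothing below depends on reproducing 182.

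**Step 2. Classify patients under each rule as written.**

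| Worsening from time 0 | END as defined (≥ 2) | END model as printed (> 2) | SND as defined (≥ 4) | SND model as printed (> 4) |
|---|---|---|---|---|
| 1 | no | no | no | no |
| 2 | **yes** | **no** | no | no |
| 3 | yes | yes | no | no |
| 4 | yes | yes | **yes** | **no** |
| 5 | yes | yes | yes | yes |

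The rules part company at exactly 2 points for END and exactly 4 points for SND.

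**Step 3. Which analyses use which rule.**
- Sequential z-test: the primary outcome, so 2 or more.
- Fisher's test on END: names END, so 2 or more.
- Fisher's test on SND: names SND, so 4 or more.
- Serious adverse event reporting and board review: 4 or more.
- Cox/Kaplan-Meier for END: more than 2 as printed.
- Cox/Kaplan-Meier for SND: more than 4 as printed.

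**Step 4. Size for END.** Let f be the share of END events that are exactly 2 points. The documents do not give f, so it is an assumption, taken as equal in both arms. With 91 per arm, and with timing and missing data treated alike in both analyses:

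expected events in the model = 91 × (0.05 + 0.20) × (1 − f) = 22.75 × (1 − f)

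| f | 0° rate | 30° rate | Expected events |
|---|---|---|---|
| 0 | 5% | 20% | 22.8 |
| 10% | 4.5% | 18% | 20.5 |
| 25% | 3.75% | 15% | 17.1 |
| 50% | 2.5% | 10% | 11.4 |

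No planning rate is given for SND, so no count can be computed for it.

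**The case against.** **The symbols may be a conversion artefact.** The Summary of Research Protocol Changes prints age, ASPECTS and Rankin criteria with > or < where the body has ≥ or ≤. An underlined > that lost its line would look just like these sentences. This stands as a reason to check the PDF. It does not remove the point: the body keeps ≥ in the site criteria, the inclusion criteria, both endpoint definitions and the adverse event section, whereas > appears in all four Cox/Kaplan-Meier sentences across the two versions. As version 2.0 repeats version 1.0, those four are not independent evidence.

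**The symbols are only glosses on defined terms.** END and SND are each defined explicitly, and many analysts would follow the definitions. That limits the weight, but the parentheses are the only event description in the sentences that specify the models.

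**The models might not count fewer END events overall.** This is correct. The Endpoints section assesses END when positioning ends and counts a missing evaluation as an event. A time-to-event analysis over 10-minute assessments may count a transient worsening and may censor an unevaluated patient. The stricter threshold by itself can only remove events, but the net difference for END could go either way.

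**Improvement would count as an event.** A reader might infer this because *change* has no direction. The documents do not support it: the sentence concerns deterioration, and the Endpoints section classes improvement as stable.

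**Conclusion.** On the text supplied, the contradiction holds for both endpoints in the current version. Read literally, the Cox and Kaplan-Meier analyses use a threshold one point stricter than the definitions. The definitions and the model sentences must be reconciled. Confidence is moderate until the symbols are checked in the PDF.

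The weight is minor to moderate. For END, the threshold alone would lower the expected 22.8 model events to between 20.5 and 11.4 for assumed shares of 10% to 50%, and would leave them unchanged if no event were exactly 2 points.

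Two stronger readings are tempting and should not be drawn:
- *The trial loses power.* The Table 2 rule is applied to the test of proportions on the primary outcome, which is END at 2 or more points. It is never applied to the stricter event, and the Cox comparison has no boundary or power target in the plan. The sample size and boundaries are untouched.
- *Four-point deteriorations escape safety oversight.* They still meet the SND definition, still trigger adverse event reporting and board review, and still enter the SND frequencies and Fisher's test. Only the SND model and curves would omit them.

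**What to change.** First check in the PDF whether the two symbols are ≥ signs with a lost underline. If they are printed as >, change two phrases:
- Analysis Plan for Aim 1, Cox/Kaplan-Meier sentence: describe the event as an *increase of 2 or more NIHSS points from the time-0 score*.
- Analysis Plan for Aim 2, Cox/Kaplan-Meier sentence: describe the event as an *increase of 4 or more NIHSS points from the time-0 score*.

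This wording also makes the direction explicit. It needs no new data and does not touch the sample size, the boundaries or the conduct of the trial. Enrolment is recorded as closed, so if the models have already been run, the report should state which threshold was programmed.

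The change aligns thresholds only. END counts in the models may still differ from those in Fisher's test because of assessment timing and the rule that a missing evaluation counts as END. A sentence saying how the time-to-event analysis treats transient worsening and unevaluated patients would let a reader reconcile the two.

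### Table 2 makes the z-test of proportions decisive, but Fisher's test and the Cox model are given no role or level, and the effect estimate makes no allowance for early stopping

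*Supplement*

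**What the plan says.** All references are to protocol v2.0.

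- **Design test.** Under Endpoints, Primary Endpoint, the group-sequential design is "based on a two-sample two-sided proportion test as implemented in East 6.0", at a type I error of 0.05. It has "80% power; it incorporates 3 interim analyses and 1 final look at the data". The assumed END rates are 5% (0°) and 20% (30°), with 182 patients.
- **Boundaries.** The Analysis Plan for Aim 1, Table 2, and Plans for Interim Efficacy and Futility Analyses all apply the boundaries to the z-value for equality of proportions. The last row of Table 2 is ±2.014.
- **Further tests.** The Analysis Plan for Aim 1 adds "We will use unadjusted Cox proportional-hazards modeling to compare and Kaplan-Meier curves to visualize the rate of early neurological deterioration", and then: "Overall rates of END and according to group will be reported as frequencies and percentages and compared between groups with Fisher's Exact test". Neither test has a boundary, a nominal level, a rank or a supportive label.
- **Effect size.** "The number needed to harm will be estimated as the inverse of the absolute risk increase". No sequentially adjusted estimate, interval or p-value is specified for the primary endpoint.
- **Direction.** Aim 1 in Specific Aims frames the hypothesis as a lower END rate at 0°, with the alternative V1 < Vc. The design test is two-sided.

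**The concern.** The z-test appears only in the design and stopping text. The sentence on reporting END by group names Fisher's test, and the Cox model is also there to compare the arms. If the three disagree at the end, the plan does not say in so many words which p-value settles Aim 1, and the choice could be made with the results in view.

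The second issue is estimation. When a trial stops because a boundary was crossed, the raw difference at that look is on average too large. The plan's absolute-effect summary, 1/ARI, takes in that error directly, and the number needed is likely to be the figure quoted in practice.

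**Working it through.** **1. The plan's own figures.** Inputs: 5% versus 20%, two-sided 0.05, 80% power, 1:1 allocation, looks at 46, 92, 138 and 182.
- Numerical integration of the efficacy bounds, ignoring futility, gives an overall two-sided alpha of 0.0500. The final ±2.014 is a nominal two-sided p of 0.0440.
- Fixed sample size per arm: (1.96·√(2·0.125·0.875) + 0.842·√0.2075)² / 0.15² = 75.1, or 150.2 in total. With continuity correction the total is 175.9 (170.4 with unpooled variance).
- Sequential inflation is 1.020 with efficacy bounds only and 1.084 with futility. So 175.9 × 1.020 = 179 and 170.4 × 1.084 = 185, which bracket the stated 182. The design is reproduced.

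**2. Can z and Fisher disagree at 91 per arm?** z = (p30 − p0) / √(2·p̄(1 − p̄)/91), with p̄ the pooled rate.

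| END, 0° vs 30° | difference | pooled z | Fisher p |
|---|---|---|---|
| 4 vs 12 | 8/91 = 8.8 points | 2.09 | 0.064 |
| 6 vs 15 | 9/91 = 9.9 points | 2.09 | 0.061 |
| 8 vs 18 | 10/91 = 11.0 points | 2.12 | 0.055 |

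Each crosses 2.014, and each has Fisher p above 0.05. For 4 vs 12: p̄ = 16/182 = 0.0879, standard error 0.0420, and 0.0879/0.0420 = 2.09.

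**3. How often?** 400,000 trials were simulated with pooled z, 23/46/69/91 per arm, and both Table 2 boundaries obeyed.
- At 5% versus 20%, 12% of trials that first cross at the final look have Fisher p of 0.05 or more, which is 2.4% of all trials. With unpooled z it is 16% of final-look crossings.
- At 5% versus 15%, it is 5.0% of all trials.
- At looks 2 and 3, every simulated crossing in favour of 0° also had Fisher p below 0.05.
- Among the tables enumerated at 91 per arm, none had Fisher p below 0.05 with |z| under 2.014. The conflict runs one way.

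The Cox disagreement was not quantified, because the documents give no distribution of event times. It could be wider, since the Cox sentence uses a change greater than 2 points while the endpoint is a worsening of at least 2 at the end of positioning.

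**4. The raw estimate after an early efficacy stop** (same simulation, true difference 15 points, true 1/ARI = 1/0.15 = 6.7).

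| Stop for efficacy | share of trials | mean observed difference | 1/mean |
|---|---|---|---|
| Look 2 | 16.4% | 24.9 points | 4.0 |
| Look 3 | 46.8% | 16.9 points | 5.9 |
| Any early look | 63% | 18.9 points | 5.3 |

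Check on the last row: (0.164 × 24.9 + 0.468 × 16.9)/0.632 = 19.0 from rounded inputs, 18.9 unrounded. The relative excess is 18.9/15 − 1 = 26%. With unpooled z, early efficacy stops reach about 66% of trials, with a similar average. Over all trials, however they end, the mean is 15.2 points.

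**The case against.** The strongest reply is that the decision test is not in doubt. The design, the worked example, both copies of Table 2 and the monitoring plan all rest on the z-value, through to the final look. Fisher's test sits in a sentence about reporting, and the directional wording of Aim 1 is a scientific hypothesis beside an explicitly two-sided test. This stands: the gap is an unstated role for the other tests, not a missing primary test.

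Three stronger readings are tempting, and the documents do not support them.

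- **Inflated type I error.** That would need a final z cut of 1.96, and the plan has 2.014. The stopping rule holds its level, and Fisher's test errs on the cautious side.
- **Ordinary 95% intervals that fail after early stops in general.** The plan specifies no interval for this comparison. If a Newcombe interval is supplied, coverage after any early efficacy stop is 97.5% at 5% versus 20% and 94.4% at 5% versus 15%. It falls to 72% only given a look-2 stop at 5% versus 15%, which has a probability of about 4.5%.
- **A typical number needed of 4.0.** That belongs to look-2 stops. Most early stops come at look 3, where the excess is modest.

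What remains is that two tests of END have no role or level, and that no estimator matches the sequential design.

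**Conclusion.** The point holds as a gap in labelling and estimation that should be closed; it does not invalidate the design. Following the text as written, the trial can report a non-significant Fisher p after crossing its own boundary. The chance is small: about 2.4% at the design rates and 5.0% if the 30° rate is 15%.

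The raw effect is on average overstated after an early efficacy stop, by about 4 points (18.9 against 15) at the design rates. The excess is marked at look 2 and about 2 points at look 3.

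These figures assume pooled z, equal arms at each look, futility stops obeyed, and END rates that already include missing assessments counted as events. The plan does not say whether z is pooled or whether the futility bounds are binding.

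**What to change.** In the Analysis Plan for Aim 1:

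1. State that the two-sided pooled z-test of proportions against Table 2, with |z| of at least 2.014 at the final look, is the sole confirmatory test of the primary endpoint.
2. Label the Fisher and Cox comparisons supportive, with no claim of success resting on either.
3. Align the alternative in Aim 1 with the two-sided test: V1 not equal to Vc, with 0° favoured as the expected direction.
4. Report a median-unbiased risk difference, and the number needed derived from it, with a 95% confidence interval by stage-wise ordering or repeated intervals. Show the naive value beside it.

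The cost is a few sentences and one standard group-sequential estimation step. No further patients or data are needed. The downside is a slightly less favourable reported effect if the trial stops early.
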